#### Withdrawal criteria

2.3.5

1.Violation of inclusion criteria and clinical trial protocol or exclusion criteria;2.Less than 30 sessions of RMS treatment were performed within 20 days;3.Serious adverse events occurred;4.Lost follow-up;5.Withdrawal of consent by subject or legal representative;6.Increase the treatment that may affect the study without the permission of the investigator.

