#### Control group

2.7.2

The control group was only given basic treatment.

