### Adverse events observation

2.8

Local skin numbness around HT7 point may be related to rMS of HT7 point. During the study, a patient treatment log will be established to monitor all adverse reactions during treatment and follow-up, and appropriate intervention will be carried out.

Patients with severe insomnia during the study were given dexzopiclone (3 mg QN). However, subjects who could not tolerate 80% of the rMS intensity and / or took more than twice a week of dexzopiclone were considered withdrawn.

In case of serious adverse reactions during the treatment, report to the principal investigator immediately, record the details in the patient treatment log and take corresponding treatment measures. If the subject or researcher thinks that the patient cannot tolerate these adverse reactions, the trial can be terminated and the subject will withdraw from the study.

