### Statistical analysis

2.13

According to the situation of data collection, data analysis will be based on the principle of intention to treat analysis and / or per protocol analysis. We will also evaluate the group effect by comparing the analysis results of the above 2 data sets to evaluate the accuracy of our analysis results.

All data will be analyzed by third-party statisticians using SPSS 23.0 (v23.0, SPSS Inc, Chicago, IL). *P* < .05 was significant. Descriptive statistics will be carried out by group and time for average, standard deviation, maximum value, minimum value, and so on.

The data in accordance with the protocol set were selected for analysis. If the data obey normal distribution, they can be described by means, and standard deviation. If the variance is uniform, the analysis of variance of complete random design can be used to compare the effect indexes. If the variance is not uniform, the rank sum test of multi group comparison of complete random design can be used. If the data does not obey normal distribution, it can be described by median and interquartile distance. The hypothesis test used the bilateral test uniformly, with *P* < .05 as the statistical significance.

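### Section 2.13 contradicts itself on the analysis set, and a per-protocol comparison can be biased because two withdrawal rules can remove only stimulation patients

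*Protocol article*

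**What the plan says.** All references are to the protocol article.

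- **Section 2.13, opening:** "data analysis will be based on the principle of intention to treat analysis and / or per protocol analysis", with the choice tied to how data collection goes. The two sets are to be set against each other, "comparing the analysis results of the above 2 data sets to evaluate the accuracy of our analysis results".
- **Section 2.13, paragraph that specifies the tests:** "The data in accordance with the protocol set were selected for analysis". Sections 2.13.1 and 2.13.2, on the primary and secondary outcomes, name no set.
- **Section 2.3.5, withdrawal criteria:** one criterion is "Less than 30 sessions of RMS treatment were performed within 20 days". Others could be met in any arm, for example "Increase the treatment that may affect the study without the permission of the investigator", loss to follow-up, a serious adverse event or withdrawn consent.
- **Section 2.8:** "Patients with severe insomnia during the study were given dexzopiclone", with no restriction by arm. In addition, "subjects who could not tolerate 80% of the rMS intensity and / or took more than twice a week of dexzopiclone were considered withdrawn".
- **Section 2.7.2:** "The control group was only given basic treatment", so controls have no stimulation sessions to miss and no intensity to tolerate.
- **Section 2.12:** the trial is open.

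**The concern.** Two problems meet here.

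First, the analysis set is not fixed. One sentence permits ITT, PP or both, depending on how data collection goes. A later one in the same section selects PP. Where the two sets give different answers, the text does not say which governs, and a choice made once the data are known is a further unplanned route to P < .05.

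Second, the events that would take a patient out of a PP set happen after randomisation and are not symmetric between arms. The session and intensity rules act on the stimulation arm alone. The rescue rule acts on patients in either arm who slept badly after randomisation. If those who leave would have scored differently from those who stay, the remaining groups are no longer comparable by design. Because the trial is open, knowledge of the arm could also influence reported tolerance and rescue use.

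The withdrawal wording also does not separate stopping treatment from leaving the study. If withdrawn patients are not tested at day 20, an ITT analysis lacks their outcomes as well, and these cannot be recovered later.

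**Working it through.** **1. The plan's own figure.** Section 2.11 gives 30 per arm and 20% loss: 30 × (1 + 0.20) = 36 per arm, 72 randomised. This reproduces the stated number. No effect size, SD or power is given, so nothing further can be reproduced.

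**2. Which arm can meet each rule**

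| Rule | Section | Stimulation | Control |
|---|---|---|---|
| Fewer than 30 sessions in 20 days | 2.3.5 | yes | no |
| 80% of intensity not tolerated | 2.8 | yes | no |
| Rescue hypnotic more than twice a week | 2.8 | yes | yes |
| Eligibility or protocol violation, serious adverse event, loss to follow-up, withdrawn consent, unapproved treatment | 2.3.5 | yes | yes |

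Only the rescue rule touches an outcome domain. That domain is sleep, which is secondary (2.10). The primary outcomes are three cognitive tests (2.9).

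**3. Slack in the session rule.** Inputs: two sessions a day, five days a week, 30 sessions (2.7.1); a 20-day study period (2.1) and a 20-day limit (2.3.5). Assumption: treatment days are weekdays.

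- Needed: 30 / 2 = 15 treatment days.
- Monday start: 20 consecutive days contain 5 + 5 + 5 = 15 weekdays, so 15 × 2 = 30 sessions.
- Tuesday start: 4 + 5 + 5 = 14 weekdays, so 28 sessions.
- Wednesday (3 + 5 + 5 + 1), Thursday (2 + 5 + 5 + 2) and Friday (1 + 5 + 5 + 3): also 14 weekdays and 28 sessions.

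On a Monday start one missed session that is not made up meets the withdrawal criterion. On any other start, full attendance meets it.

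**4. Possible size of the bias.** The document gives neither removal shares nor their link to outcome, so both are assumed. Model: no true effect, 36 per arm, a normally distributed outcome, and a tendency to stay in that has correlation ρ with the outcome. The lowest fraction q on that tendency is removed. The mean of those kept is then shifted by ρ·φ(z_q)/(1 − q), and the bias is the difference in shifts between arms.

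- q = 0.20: φ(−0.842)/0.80 = 0.280/0.80 = 0.350
- q = 0.05: φ(−1.645)/0.95 = 0.103/0.95 = 0.109
- q = 0.10: φ(−1.282)/0.90 = 0.1755/0.90 = 0.195

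20% v 5% removed (stimulation v control): ρ × (0.350 − 0.109) = 0.241ρ, which is 0.072 SD at ρ = 0.3 and 0.145 SD at ρ = 0.6.

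10% v 20% removed: ρ × (0.195 − 0.350) = −0.155ρ, which is −0.046 and −0.093 SD.

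The rejection rate comes from 5,000 simulated trials per row, with a two-sided t test at 0.05 on one outcome:

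| Removed, stimulation v control | ρ | Bias (SD) | Type I error |
|---|---|---|---|
| 20% v 20% | 0.3 / 0.6 | 0 / 0 | 4.8% / 4.5% |
| 20% v 5% | 0 | 0 | 5.6% |
| 20% v 5% | 0.3 / 0.6 | 0.072 / 0.145 | 6.3% / 9.1% |
| 10% v 20% | 0.3 / 0.6 | −0.046 / −0.093 | 5.2% / 6.6% |

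The Monte Carlo standard error near 5% is √(0.05 × 0.95 / 5,000) = 0.3 percentage points, so the rows with zero bias are compatible with 5%.

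**The case against.** The other side has a fair case. Section 2.13 names ITT first and promises to compare both sets, so a generous reader may take it that both will be run. No section defines the PP set; tying it to the rules in 2.3.5 and 2.8 is an inference, and the formal definition may properly sit in an analysis plan that is not shown. Comparing ITT with PP is an ordinary sensitivity check, and the text does not say that agreement proves accuracy. The Discussion also calls the study a pilot.

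These points limit the finding but do not remove it. The contradiction lies in the printed text, and the link between withdrawal and the PP set is the natural one. The Discussion also says that the trial intends to confirm a benefit.

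Three stronger readings are tempting, and the documents do not support them.

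- **That PP is settled as the analysis set and the result is biased in favour of stimulation.** The ITT option is in the same section. The rescue rule and most of 2.3.5 apply to both arms. If stimulation helped sleep, the rescue rule could remove more controls and reverse the sign.
- **That patients are removed on the trial's outcome.** Only the rescue rule concerns an outcome domain, and it is not one of the primary cognitive tests.
- **That the strict session rule implies a very large bias.** With a 2% chance of missing each session, 0.98^30 = 0.55, so about 45% of the stimulation arm would be excluded. Independent random misses are unrelated to prognosis, so under that model ρ = 0 and the bias is nil. That share shows how many patients the rule could cost, not how far it would shift the comparison.

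**Conclusion.** The concern holds in this form: the analysis set is contradictory and open to a late choice, and a PP comparison shaped by these rules can be biased. The arm-specific nature of the session and intensity rules is certain from the text. The size and direction of any bias are not. The figures of about 0.07 to 0.15 SD and 6 to 9% type I error rest on the assumed 20% v 5% removal, ρ of 0.3 to 0.6, a normal outcome and a t test (the plan names analysis of variance, rank sum or chi-squared tests). They show what could happen and do not predict it. The lack of slack in the session rule follows from the document's own numbers once treatment days are taken to be weekdays.

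**What to change.** 1. In 2.13, replace the either-or wording and the sentence that selects the protocol set with one statement: the primary analysis is ITT, with all randomised patients analysed in their assigned arm.
2. State that patients who meet a rule in 2.3.5 or 2.8 and still consent are tested at day 20. Record sessions delivered, intensity tolerance and rescue use as adherence or intercurrent-event data, so that stopping treatment is separate from leaving the analysis.
3. Keep PP as a labelled sensitivity analysis, and describe the ITT/PP comparison as a sensitivity check, not as a test of accuracy.
4. The sponsor must reconcile the 20-day, five-days-a-week and 30-session statements in 2.1, 2.3.5 and 2.7.1. This review does not say which should change.

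Cost: a few sentences, a few extra day-20 assessments, and possibly a smaller treatment estimate than PP would give.

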#### Primary outcomes

2.13.1

On the day of admission and the 20th day of treatment, the patients will be evaluated with

1-back working memory,

Rey osterieth complex figure test and

Hanoi tower test, and the obtained data will be used by rank sum test or Chi-squared test.

After statistical analysis between groups, the significant influence between groups will show that the 1-back working memory, Rey osterieth complex figure test, Hanoi Tower test there are differences.

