**Methods/Design::**

This is a randomized controlled clinical trial. Seventy-two subjects aged 18 to 65 years old with primary insomnia and more than 3 months were randomly divided into 2 groups according to the ratio of 1:1, and 36 healthy controls were included. The control group was given sleep hygiene and cognitive therapy in behavioral cognitive therapy technology, while the experimental group was given the behavioral cognitive therapy technology intervention and magnetic stimulation of HT7 acupoint for 30 times (2 times / d, 5 times / wk for 20 days), while the healthy control group had no intervention measures. Before treatment and 20 days after treatment, we evaluated the working memory (1-back test), episodic memory (Complex Figure Test), and problem-solving ability (Hanoi tower test) processed by prefrontal lobe to explore the effect of magnetic stimulation on cognitive function of CI and its possible mechanism. At the same time, insomnia severity index was used to evaluate sleep state, Becker depression scale was used to evaluate depression, and Beck anxiety scale was used to evaluate anxiety. Chi-squared test or rank sum test was used to collect the data of patients. If *P* value is less than or equal to .05, the difference will be considered statistically significant.

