### Primary outcomes

2.9

The cognitive function of the patients was evaluated on the day of enrollment and the 20th day after treatment:

1.1-back working memory;2.Rey osterieth complex figure test;3.Hanoi tower test.

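### The general and primary-outcome sections name different tests for the same outcomes, and neither fixes the contrast, the variable analysed or the use of baseline

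*Protocol article*

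**What the plan says.** Section 2.13 (Statistical analysis) gives the general rule. For normal data, "If the variance is uniform, the analysis of variance of complete random design can be used to compare the effect indexes". If variances are not equal, "the rank sum test of multi group comparison of complete random design can be used". For non-normal data it gives a summary and no test: "If the data does not obey normal distribution, it can be described by median and interquartile distance".

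Section 2.13.1 covers the 1-back, complex figure and Hanoi tower tests, measured at admission and day 20. There, "the obtained data will be used by rank sum test or Chi-squared test". ANOVA is absent and nothing says when each test applies. The abstract matches this section: "Chi-squared test or rank sum test was used to collect the data of patients". Section 2.13.1 then adds that "the significant influence between groups will show that the 1-back working memory, Rey osterieth complex figure test, Hanoi Tower test there are differences", without saying which groups.

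Section 2.9 confirms the two time points: "The cognitive function of the patients was evaluated on the day of enrollment and the 20th day after treatment". Section 2.1 randomises 72 patients 1:1 and adds 36 healthy people who receive no intervention. Section 2.12 describes the trial as open.

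**The concern.** The trial asks whether magnetic stimulation of HT7 added to basic treatment improves cognition over basic treatment alone. The test, the contrast and the variable for that question should be settled before data are seen, especially in an open trial. Here they are open in five respects.

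- **Test.** ANOVA appears only in section 2.13 and chi-squared only in the abstract and section 2.13.1. Rank sum is common to both, but as a multi-group test in one and with no groups stated in the other.
- **Scale.** Chi-squared needs categories, and none are defined for any of the three tests.
- **Variance rule.** A rank sum test is no remedy for unequal variances. Its null hypothesis is identical distributions, so differing spread disturbs it as well.
- **Contrast.** No section names experimental versus control as the primary comparison.
- **Variable and baseline.** No section says whether the day-20 score or the change is tested, and no named test has a baseline term.

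At stake are a free choice among analyses after the data are in, a significant result that may not concern the treatment at all, and power lost in a small trial.

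**Working it through.** **The passages side by side**

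| Item | Section 2.13 | Section 2.13.1 and abstract |
|---|---|---|
| Normal, equal variance | one-way ANOVA | rank sum or chi-squared |
| Normal, unequal variance | multi-group rank sum | rank sum or chi-squared |
| Not normal | summary only, no test | rank sum or chi-squared |
| Groups compared | multi-group (rank sum branch) | not named |
| Variable tested | not stated | not stated |
| Baseline adjustment | none | none |

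**Inputs.** Section 2.11 starts from 30 per group and allows 20% loss: 30 × 1.2 = 36, which reproduces its stated figure. Results are given for 30 and 36 per group. Alpha is 0.05 two-sided (section 2.13). The document gives no effect size, SD, healthy–patient difference or baseline correlation, so all of these below are assumptions, in SD units.

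**1. A three-group test when the treatment does nothing.** Let both patient arms have mean 0 and the healthy group mean h, with SD 1 and n per group. The grand mean is h/3, so the ANOVA noncentrality is

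λ = n[2(h/3)² + (2h/3)²] = 2nh²/3.

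The rejection rate is the probability that a noncentral F with 2 and 3n − 3 degrees of freedom exceeds the 5% critical value.

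| h (assumed) | n = 30: λ | n = 30: rejects | n = 36: λ | n = 36: rejects |
|---|---|---|---|---|
| 0.3 | 1.80 | 20% | 2.16 | 24% |
| 0.5 | 5.00 | 49% | 6.00 | 57% |
| 0.8 | 12.80 | 89% | 15.36 | 94% |
| 1.0 | 20.00 | 98% | 24.00 | 99% |

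A simulation of 10,000 trials per setting agrees. At 30 per group, ANOVA and Kruskal–Wallis rejected 49% and 46% for h = 0.5, and 89% and 87% for h = 0.8. At 36 the figures were 56% and 54%, then 94% and 93%. A two-group rank sum test of experimental versus control rejected 4.5–5.1% throughout, whatever h was.

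**2. What the choice of variable costs.** Take a true effect of d = 0.5 SD and baseline-to-day-20 correlation r (both assumed). The standardised effect is d for day-20 scores, d/√(2(1 − r)) for changes, and d/√(1 − r²) for ANCOVA. Power comes from the noncentral t with noncentrality (standardised effect) × √(n/2).

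| Analysis | Standardised effect | Power, n = 30 | Power, n = 36 |
|---|---|---|---|
| Day-20 score | 0.500 | 48% | 55% |
| Change, r = 0.5 | 0.500 | 48% | 55% |
| Change, r = 0.7 | 0.645 | 69% | 77% |
| ANCOVA, r = 0.5 | 0.577 | 59% | 68% |
| ANCOVA, r = 0.6 | 0.625 | 66% | 74% |
| ANCOVA, r = 0.7 | 0.700 | 76% | 83% |

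**The case against.** The strongest reply is that the healthy controls are brought in by inference. The multi-group wording occurs only in the unequal-variance branch of section 2.13 and is permissive. Sections 2.9 and 2.13.1 speak of patients, no section says that healthy people are assessed at day 20, and the rank sum test of section 2.13.1 could be a two-group test. This stands. A reader might infer that the plan puts healthy controls into the efficacy test, but the text does not say so. The rejection rates above are therefore conditional on that reading.

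Three other strong readings also go beyond the text:

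- **That baseline is ignored.** Section 2.13.1 mentions both assessments, and a rank sum test on changes is not excluded. What can be said is that the variable is unstated and no named test adjusts for baseline.
- **That any significant omnibus result will be taken as proof of benefit.** The sentence says only that differences will be shown. It mentions neither an omnibus p-value nor efficacy.
- **That scores will be dichotomised.** No cut-point is proposed, so no power loss from a particular split can be attributed to the plan.

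It is also fair that an unadjusted comparison of randomised arms is valid, that covariate adjustment may be left to a fuller analysis plan, and that the Discussion calls the study a pilot. ANCOVA is therefore a recommendation, and its absence is not an error.

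None of this removes the conflict. The document states the tests for the primary outcomes in two places, and the statements do not agree. The Discussion also intends to confirm benefit.

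**Conclusion.** The point holds in this form. Section 2.13 on one side, and section 2.13.1 with the abstract on the other, name incompatible tests for the same primary outcomes. There is no rule for choosing, no categories that would permit chi-squared, no named contrast and no stated variable. That conclusion rests on the text alone.

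The size of the healthy-control risk is conditional. Since only two groups are randomised, a multi-group comparison most naturally includes the third. If it does, and the healthy group is better by an assumed 0.5 or 0.8 SD, the ANOVA rejects about 49% or 89% of the time at 30 per group (57% or 94% at 36) with no treatment effect, against about 5% for the randomised contrast. The direction is plausible on the document's own account, since the Introduction and Discussion describe cognitive impairment in chronic insomnia. The amount is not given.

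The gain from baseline adjustment is likewise an illustration. At an assumed 0.5 SD effect and correlations of 0.5 to 0.7, power rises from 48% on unadjusted day-20 scores to 59–76% at 30 per arm (55% to 68–83% at 36).

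**What to change.** Replace the competing statements in section 2.13, section 2.13.1 and the abstract with one rule:

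1. For each primary outcome, name the one score to be analysed.
2. State experimental versus control, in the randomised patients only, as the primary contrast.
3. Analyse the day-20 score by ANCOVA on arm plus the same test's baseline score. Report the adjusted mean difference with a 95% confidence interval, using a robust or bootstrap interval if residuals are skewed.
4. Delete chi-squared and the variance pre-test for these scores.
5. Report healthy controls separately as a descriptive reference, outside the efficacy test.

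No new patients, visits or measurements are needed: baseline scores are already collected, and the model runs in the SPSS version named. The cost is analysis wording, plus the decision on one score per test, which section 2.9 does not give. Section 2.13.2 repeats the rank sum or chi-squared wording for the secondary outcomes and should be aligned at the same time.

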#### Secondary outcomes

2.13.2

The patients were evaluated with insignia severity index, Becker depression scale and Beck Anxiety Scale on the day of enrollment and the 20th day of treatment, and the data were analyzed by rank sum test or Chi-squared test.

### Safety evaluation

2.14

Adverse events recorded in the patient's diary will be analyzed as a multiplicative variable. The number and percentage of AE patients will be calculated and compared using Chi-squared test

### Quality control

2.15

During the whole treatment and follow-up process, patients’ withdrawal and the reasons for withdrawal will be recorded in time. In order to ensure the test quality, the quality supervisor will regularly check all process details and check the authenticity of the data. In addition, the scientific research department of Shaanxi Provincial Hospital of traditional Chinese medicine will be invited to manage the data independently.

As differences between doctors may lead to errors, each evaluation of the scale will be performed by a designated physician trained in the same evaluation criteria. The 2 doctors in charge of the treatment will receive special training on research and operation, including the use of RMS and acupoint positioning. In order to record the patient's treatment and compliance, we made a record card for the patient, including the treatment date, personal information and signature after each treatment.

## Discussion

3

Sleep is an important part of human life activities. It can eliminate fatigue, enhance immune function, regulate emotion, and regulate cognitive function. Ci can not only lead to sub-health status, but also lead to damage in many cognitive fields, which brings serious harm to patients and society. No matter whether CI has cognitive impairment or not, cognitive function has been impaired to a certain extent.^[2]^

Neurocognitive deficits after CI are caused by neurobiological changes.^[17]^ Compared with healthy people, the regional homogeneity of the upper right medial prefrontal cortex was significantly different in CI patients; and the more serious the cognitive impairment, the greater the homogeneity difference of the dorsolateral cortex of the right prefrontal cortex.^[18]^ A voxel based fMRI morphometric study found that the volume of the left orbitofrontal Gray matter in insomnia patients decreased, and it was closely related to the subjective severity of insomnia.^[19]^ The microstructure of prefrontal cortex in insomnia patients is damaged, which affects the emission of brain nerve impulses and signal transmission, resulting in insufficient activation of cognitive processing and dysfunction of brain functional connectivity, which may be an important neurobiological process of Ci and its accompanying cognitive impairment.

RTMS and traditional Chinese medicine acupuncture and moxibustion are commonly used in CI treatment, and have significant curative effect. Compared with rTMS, RMS has fewer contraindications. Compared with acupuncture, RMS has the advantages of noninvasive and painless, which can reduce the pain of patients and increase the compliance of patients. In this study, rMS was combined with acupuncture and moxibustion of traditional Chinese medicine, and HT7 was used to intervene cognitive impairment of CI. The purpose of this study is to observe the clinical efficacy of magnetic stimulation of HT7 on cognitive impairment in patients with CI through the evaluation of cognitive function, sleep quality, and emotion of CI patients, and analyze the possible mechanism.

Our scheme is only a pilot study, so there may be problems in sample size and observation time. In the course of the experiment, we will try our best to reduce the deviation that affects the research results. Finally, we intend to confirm that magnetic stimulation of HT7 can be used as an alternative therapy to improve cognitive impairment of CI.
